### From 24 to 48 hours

The infusion protocol will be modified as below according to the sNa levels at every sample time point (at 30, 36, 42, and 48 h). If the Na level increases to 10–17 mmol/L above the initial sNa level or sNa reaches 130 mmol/L, and symptom relief is observed, the 3% hypertonic saline infusion should be discontinued regardless of changes in the sNa level during the previous 6 h. If the Na level increase is less than 1.5 mmol/6 h, it is recommended to add 3% hypertonic saline infusion at a rate of 0.25 mL/kg/h to the previous infusion rate or to restart the infusion at a rate of 0.25 mL/kg/h if it was previously discontinued. If sNa levels increase at a rate of over 1.5 mmol/6 h, the 3% saline infusion rate should be maintained.

### Outcome measures

The primary outcome is the incidence of overcorrection, a surrogate marker of ODS, at any given period, defined as follows: increase in sNa level by >12 mmol/L within the first 24 h or increase in sNa level by >18 mmol/L within 48 h. The secondary outcomes will include efficacy and safety; changes in symptoms between pretreatment and 24 and 48 h after treatment with 3% hypertonic saline; time from treatment initiation to an increase in sNa ≥5 mmol/L; time from treatment initiation to the achievement of a sNa >130 mmol/L; incidence of target correction rate, defined as an achieved sNa <10 mmol/L within 24 h and a sNa <18 mmol/L within 48 h; length of hospital stay; incidence of additional treatment; incidence of ODS confirmed by the *International Classification of Disease, 10th Revision (ICD-10)* code or magnetic resonance imaging (MRI); incidence of relowering treatment; and change in GCS score between pretreatment and 24 and 48 h after 3% hypertonic saline treatment.

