### Study participants and measurements

All participants will be selected from among patients visiting the emergency rooms of two general hospitals in Korea (Seoul National University Bundang Hospital, Seoul National University Boramae Medical Center). Patients aged over 18 years who have moderately severe to severe symptoms and glucose-corrected sNa [25] ≤125 mmol/L on the first blood test will be screened for study participation. Moderate symptoms include nausea, headache, drowsiness, general weakness, and malaise [1, 26, 27]. Severe symptoms include vomiting, stupor, seizure, and coma (Glasgow Coma Scale (GCS)).

The following assessments will be performed during the initial emergency room encounter: (1) completion of questionnaire on medical and drug history including the use of antihypertensive medication, diuretics, nonsteroidal anti-inflammatory drugs, selective serotonin reuptake inhibitors, antiepileptic drugs, steroids, and synthyroid, (2) physical examination of all body systems, (3) measurement of height and weight, (4) blood pressure and pulse rate measurement, and (5) assessment of psychological status. Participants, who meet all of the inclusion criteria, do not require exclusion on the basis of the exclusion criteria, and provide written informed consent will be eligible for this study (Table 1).

**Table 1 Tab1:** Inclusion and exclusion criteria

Inclusion criteria	Exclusion criteria
18 years and older	Pseudo-hyponatremia (serum osmolality >275 mOsm/kg)
	Primary polydipsia (urine osmolality ≤100 mOsm/kg)
	Glucose-corrected serum sodium >125 mmol/L
	Initial arterial hypotension (SBP <90 mmHg and MAP <70 mmHg)
Glucose-corrected serum sodium ≤125 mmol/L	Anuria or urinary outlet obstruction
	Decompensated LC (LC with ascites or diuretics use or history of hepatic encephalopathy and varices)
	Bilirubin >2 mg/dL, transaminase levels >2.5 times the upper limit of normal)
Symptomatic patients	Uncontrolled diabetes mellitus (HbA1C >9%)
Moderately severe:	Women who are pregnant or breastfeeding
nausea without vomiting, drowsiness, headache, general weakness, malaise	Within the 3 months prior to randomization, history of cardiac surgery excluding PCA, acute myocardial infarction, sustained ventricular tachycardia, ventricular fibrillation, acute coronary syndrome, cerebrovascular trauma, and increased intracranial pressure
Severe:	
vomiting, stupor, seizures, coma (GCS ≤8)	

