### Physician’s practical treatment guidelines according to the sNa level

The principal purpose of this study will be to compare the rapid intermittent correction group to the slow continuous correction group [29]. According to a review of the medical literature on the treatment of hyponatremia, treatment with hypertonic (3%) saline is recommended in cases of severe symptomatic hyponatremia [1, 15, 16]. Therefore, the rate of infusion of 3% saline will be stratified based on the symptom severity in each group. After randomization, the participants will undergo either rapid intermittent correction or slow continuous correction of hyponatremia for 48 h. Treatment in the intermittent bolus group will comply with European guidelines published in 2014, and the slow continuous infusion will be guided by widely accepted methods [1, 13–16]. The treatment goals are to raise the sNa level by 5–9 mmol/L from the initial sNa and to achieve symptom relief within the first 24 h, and to raise the sNa level by 10–17 mmol/L from the initial sNa or ≤130 mmol/L, and to achieve symptom relief during the 48 h [10–12]. We will also check for overcorrection at every sample time point and conduct relowering treatment. Relowering treatment is performed as below if the achieved sNa level is ≥10 mmol/L at any sample time point within the first 24 h or the achieved sNa level is ≥18 mmol/L at any sample time point within 48 h [1, 13–16]. The treatment goal, relowering treatment strategy, and cause-specific treatment of hyponatremia will be applied to each group equally.

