### From 24 to 48 hours

In both moderately severe and severe cases of hyponatremia, repeated infusion of 2 mL/kg 3% hypertonic saline over 20 min at every sample time point (at 30, 36, 42, and 48 h) is recommended until the sNa level increases to 10–17 mmol/L from the initial sNa or until the sNa reaches 130 mmol/L, and until the symptoms improve.

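### The secondary outcome that times sodium above 130 mmol/L does not match the plan's 48-hour goal or stop level, and from low baselines it coincides with the primary harm event

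*Protocol article*

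**What the plan says.** All references are to the protocol article.

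- **Outcome.** Outcome measures lists, among secondary outcomes introduced as covering efficacy and safety, "time from treatment initiation to the achievement of a sNa >130 mmol/L". No time limit is attached. Statistical analyses then names a time to the target sodium without defining it. The only sodium times in Outcome measures are this one and the time to a rise of 5 mmol/L, so the target is most naturally this outcome.
- **Goal.** The section on practical treatment guidelines sets the 48-hour goal as "to raise the sNa level by 10–17 mmol/L from the initial sNa or ≤130 mmol/L", with symptom relief.
- **Stop level on day 2.** In the bolus group, boluses repeat until a rise of 10–17 mmol/L "or until the sNa reaches 130 mmol/L, and until the symptoms improve". In the continuous group, if the rise is 10–17 or "sNa reaches 130 mmol/L, and symptom relief is observed, the 3% hypertonic saline infusion should be discontinued".
- **Stop level on day 1.** Both groups stop at a rise of 5–9 mmol/L with symptom relief.
- **Primary event.** Overcorrection, used as a surrogate for osmotic demyelination, is an "increase in sNa level by >12 mmol/L within the first 24 h" or an "increase in sNa level by >18 mmol/L within 48 h".
- **Eligibility.** Patients are screened with "glucose-corrected sNa [25] ≤125 mmol/L on the first blood test". No lower limit is stated.
- **Sampling.** Sodium is measured every 6 h for 2 days.

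**The concern.** The goal is at or below 130, treatment ends on reaching 130, and the outcome begins above 130. A patient who stops at exactly 130 with symptoms relieved has met the goal but not the outcome.

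The outcome is a fixed level, whereas the harm definition is a rise from baseline. The lower the starting sodium, the larger the rise needed to pass 130, and below some baseline that rise is itself the primary event. One sodium value would then count as an achievement on a secondary outcome and as harm on the primary. A shorter time is naturally read as better. An arm that overcorrects more often could therefore look faster on this outcome partly because of the same patients who count against it on the primary.

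**Working it through.** The plan attaches no figure to this outcome, so there is none to reproduce. The check is threshold arithmetic on the stated limits.

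**Inputs.** Outcome: above 130. Primary event: rise >12 in 24 h or >18 in 48 h. Relowering trigger (practical guidelines and Safety issues, read here as a rise): ≥10 in 24 h or ≥18 in 48 h. Target ranges: rise 5–9 on day 1, 10–17 by 48 h. Eligible baseline: ≤125.

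**Step 1: stop level against outcome.** With symptom relief, the stop condition is first met at baseline + 5 on day 1, which is at most 125 + 5 = 130. On day 2 it is first met at the lower of baseline + 10 and 130. For every eligible baseline it can therefore be met at or below 130, while the outcome needs more than 130.

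**Step 2: rise needed.** In whole mmol/L, the smallest qualifying value is 131, so rise = 131 − baseline.

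| Baseline | Rise to 131 | If reached within 24 h | If reached from 24 to 48 h |
|---|---|---|---|
| 112 | 19 | primary event | primary event |
| 113 | 18 | primary event | no primary event, but relowering trigger |
| 114 | 17 | primary event | within 10–17 |
| 118 | 13 | primary event | within 10–17 |
| 119 | 12 | no primary event, but relowering trigger | within 10–17 |
| 121 | 10 | no primary event, but relowering trigger | within 10–17 |
| 122 | 9 | within 5–9 | no primary event |
| 125 | 6 | within 5–9 | no primary event |

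The two primary-event cut-offs do not depend on rounding: 130 − 112 = 18, so anything above 130 is a rise >18, and 130 − 118 = 12, so anything above 130 is a rise >12.

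**Step 3: how many baselines are affected.** The documents give no baseline distribution. Assume a normal with mean 116–120 and SD 4–6, truncated at 125. The share at or below c is Φ((c − mean)/SD) ÷ Φ((125 − mean)/SD).

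- ≤112: lowest at mean 120, SD 4 (0.0228/0.8944 = 2.5%); highest at mean 116, SD 6 (0.2525/0.9332 = 27.1%).
- ≤118: lowest at mean 120, SD 4 (0.3085/0.8944 = 34.5%); highest at mean 116, SD 4 (0.6915/0.9878 = 70.0%).
- With a half-unit correction for whole-number values (112.5, 118.5 and 125.5), the ranges are 3.3–29.7% and 38.7–74.1%.

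Together these are very roughly 3–30% and 34–74%. They are shares of baselines, not of patients who would exceed 130.

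**Step 4: a ceiling on double counting.** A patient counted both ways must have a primary event. At the planning rates in Sample size calculation, expected events are 0.05 × 89 = 4.5 in the bolus arm and 0.20 × 89 = 17.8 in the continuous arm. At most about 22 of 178 patients could then be counted both ways, and the actual number would be smaller wherever overcorrection occurs without passing 130.

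**The case against.** A reader might infer that only overshooters can meet this outcome and that patients treated to plan never do. The documents do not support that. From 120, a rise of 12 on day 2 gives 132, which is inside the 48-hour range and meets the outcome. From 122–125, a value of 131 lies in the day-1 range. The stop rules also require symptom relief, sampling is 6-hourly and both arms receive cause-specific treatment, so values above 130 can occur with full adherence.

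Nor does every attainment from a low baseline have to be a primary event. The outcome has no time limit, and a value above 130 after 48 h is not overcorrection, although no sodium sampling is scheduled then. From 114–118, 130 can be passed on day 2 within the goal.

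It would also go too far to say that the outcome cannot be read beside the primary. It is listed under efficacy and safety together, and overcorrection, target correction rate and relowering are reported with it, so an arm that is fast because it overshoots would be visible. Dependence on baseline applies to both randomized arms and does not by itself bias the comparison.

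These points stand and narrow the concern. They do not remove the mismatch around 130 or the overlap with the primary event at low baselines.

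**Conclusion.** The point holds for part of the population. The three uses of 130 do not agree. Reaching more than 130 is always a primary event from baseline ≤112 within 48 h, and from baseline ≤118 within the first 24 h. These cut-offs follow from the protocol's own limits and need no assumption.

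How many patients this touches is unknown. The baseline shares rest entirely on the assumed truncated normal, and the ceiling of about 22 patients rests on the planning rates. The primary outcome, sample size and interim rule are unaffected. This is a low-cost improvement to one secondary outcome.

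**What to change.** 1. Reconcile the level across the practical treatment guidelines, both 24-to-48-hour sections, Outcome measures and Statistical analyses, so that goal, stop level, timed outcome and the undefined target sodium are consistent or the differences are explained. Which level is clinically right is for the investigators; none is proposed here.
2. Analyse the time outcome so that a patient who meets the overcorrection definition at any sample within 48 h, whether before or after reaching the level, is scored as not having achieved it. Covering both orders matters: a patient sampled at a rise of 11 and then 14 on day 1 could otherwise count as an achiever and a primary event.
3. Keep the raw time to more than 130 as a descriptive figure only.

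Both of the first two steps are needed. If the level stayed above 130, step 2 alone would make everyone with baseline ≤112 a non-achiever within the sampling window by construction. Simply timing the 48-hour goal instead would not be enough either, because a rise of 10–12 on day 1 would count as fast success while triggering relowering.

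**Cost.** A wording change to one secondary outcome and its registry entry. The sodium values are already collected, and no treatment rule is changed or proposed.

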## Background

Hyponatremia is the most common electrolyte imbalance encountered in clinical practice, and is associated with increased mortality and length of hospital stay [1]. The symptoms related to hyponatremia span a broad range from moderately severe (cognitive test abnormalities, gait impairment) to severe or life-threatening (hypoxemia, coma, and epilepsy) [2–5]. Treatment strategies for hyponatremia differ according to the severity of clinical symptoms and duration of hyponatremia [6]. The extent and rate of increase in serum sodium (sNa) levels during treatment are crucial. Overcorrection of chronic hyponatremia may result in osmotic demyelination syndrome (ODS), whereas undercorrection may be insufficient to prevent its life-threatening manifestations [6–9].

Several methods for continuous infusion of hypertonic saline have been used to guide the rate of fluid administration to achieve the required sNa target [10, 11]. The increase in sNa should be limited to 8–10 mmol/L within the first 24 h and 18 mmol/L within 48 h [11, 12]. As these methods were based on static models of a dynamic clinical situation, they had a bias toward overcorrection of hyponatremia [1, 13–15].

Recent guidelines have recommended prompt infusion of 100–150 mL of 3% saline over 10–20 min to increase the sNa by 4–6 mmol/L during the first hour. A pragmatic approach to treatment with hypertonic fluid is to use small, fixed boluses to achieve controlled incremental increases in sNa [1, 13–17]. However, this recommendation was the result of small randomized trials [18], case reports with small numbers of patients [14, 19], and expert opinion [20–23]. No high-quality evidence has been reported regarding whether hypertonic saline is best administered as a continuous infusion (preferred by most) or as a rapid intermittent bolus injection. The purpose of the present study was to investigate the efficacy and safety of rapid intermittent correction compared with slow continuous correction with hypertonic saline in patients with symptomatic severe hyponatremia. Furthermore, the study will examine prevailing conceptions regarding the optimal treatment of severe symptomatic hyponatremia.

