### Safety issues

All adverse events related to overcorrection will be recorded and followed up during the study period or until resolution during treatment with 3% hypertonic saline. Any serious adverse events will be reported to investigators and the Ethics Committee. We will check for overcorrection at every sample time point and conduct relowering treatment as needed. Relowering treatment is performed as follows if the achieved sNa level is ≥10 mmol/L at any sample time point within the first 24 h or if the achieved sNa level is ≥18 mmol/L at any sample time point within 48 h: discontinuing ongoing active treatment; initiating infusion of 10 mL/kg of 5% dextrose over 1 h; and/or adding desmopressin 2 mcg [1].

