### Statistical analyses

Statistical analyses will be performed on both per-protocol (PP) and intention-to treat (ITT) bases. For the PP analysis, all participants who completed the study will be included to evaluate the primary and secondary outcomes. For the ITT analysis, all participants who were enrolled and randomized to one of the two groups will be included. The baseline characteristics and laboratory data will be presented as means and standard deviations for continuous variables and as frequencies and percentages for categorical variables.

The incidence of overcorrection, ODS, relowering treatment, and target correction rate (achieved sNa <10 mmol/L within the first 24 h and sNa <18 mmol/L within 48 h) will be compared between the two groups using a *χ*
^*2*^ test and Fisher’s exact test. In interim analysis, if the *P* value < 0.003 then we would stop the study early for significance of outcome. If not, we would recruit another half of subjects. The differences in changes in symptoms and GCS scores between pretreatment and 24 and 48 h, time to reach target sNa, time to achieved sNa ≥5 mmol/L for the first time, and length of hospital stay will be analyzed using Student’s *t* test or the Mann-Whitney *U* test. A value of *P* < 0.05 will be considered statistically significant. All analyses will be performed using SPSS Statistics software V21.0 (IBM Corporation, Armonk, NY, USA).

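### The target correction rate has no lower limit when read as a rise in serum sodium, and no patient can meet it when read literally

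*Protocol article*

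**What the plan says.** Outcome measures in the protocol article defines the outcome as "incidence of target correction rate, defined as an achieved sNa <10 mmol/L within 24 h and a sNa <18 mmol/L within 48 h". Statistical analyses repeats it as "target correction rate (achieved sNa <10 mmol/L within the first 24 h and sNa <18 mmol/L within 48 h" and compares it between arms with a χ² test and Fisher's exact test, so it is a yes/no outcome per patient.

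The goals that treatment aims for are in the section on physicians' practical treatment guidelines. For the first day: "The treatment goals are to raise the sNa level by 5–9 mmol/L from the initial sNa", together with symptom relief. For 48 h: "to raise the sNa level by 10–17 mmol/L from the initial sNa or ≤130 mmol/L", again with symptom relief. Both rises have a lower as well as an upper end.

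The relowering trigger, under Safety issues and in the treatment guidelines, uses the same cut-offs from the other side and the same wording about an achieved level: "if the achieved sNa level is ≥10 mmol/L at any sample time point within the first 24 h", or 18 mmol/L or more within 48 h.

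Elsewhere the article words such limits as a change. The primary outcome is an "increase in sNa level by >12 mmol/L within the first 24 h or increase in sNa level by >18 mmol/L within 48 h", and the Background says: "The increase in sNa should be limited to 8–10 mmol/L within the first 24 h and 18 mmol/L within 48 h".

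**The concern.** An outcome named for reaching a target should separate patients who reached it from those who fell short and those who overshot. This one separates only the overshooters.

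That matters because the primary outcome also counts only overcorrection. An arm that raises sodium too little cannot be penalised by either measure. The Background itself warns that undercorrection may fail to prevent life-threatening manifestations. A published on-target percentage would naturally be read as the share of patients treated to goal, and the definition does not measure that.

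The outcome also adds little. Because it shares its cut-offs with the relowering trigger, it largely mirrors the incidence of relowering treatment, which is already a secondary outcome.

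The wording as an achieved level is a second, independent defect.

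**Working it through.** **Figures in the plan.** None is stated for this outcome. The sample size belongs to the primary outcome (20% v 5%, two-sided 5%, power 80%, dropout 15%). The usual two-proportion formula with pooled variance gives 75.1 per group, and 75.1 / 0.85 = 88.4, rounded up to the stated 89. Nothing below changes it.

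**Inputs.** Entry requires glucose-corrected sodium of 125 mmol/L or less (Study participants and measurements). Upper limits are <10 and <18 (Outcome measures). Goals are rises of 5–9 and of 10–17 mmol/L, or the 130 mmol/L criterion (treatment guidelines).

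**Step 1: classify test patients.** Rises are the highest within each window. The goal column covers sodium only, takes 5 ≤ rise < 10 and 10 ≤ rise < 18, and counts reaching 130 mmol/L as meeting the 48 h goal.

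| Initial sodium | Rise in 24 h | Rise in 48 h | Literal level | Rise, upper limits only | Goals |
|---|---|---|---|---|---|
| 118 | −2 | −1 | no | **yes** | no |
| 118 | 0 | 0 | no | **yes** | no |
| 118 | 3 | 6 | no | **yes** | no |
| 118 | 7 | 12 | no | yes | yes |
| 118 | 11 | 16 | no | no | no |

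The first three patients miss both goals and still count as on target. In the literal column nobody succeeds: 118 is not below 10, and no plausible sodium value is. Incidence would be 0% in both arms.

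The two defects belong to different readings. The non-responder counted as a success comes from the missing lower limit on the rise reading, not from the literal wording.

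**Step 2: compare with the relowering trigger.** On target means <10 within 24 h *and* <18 within 48 h. The trigger is ≥10 within 24 h *or* ≥18 within 48 h. Each is the logical complement of the other, so on target means only that the trigger was never reached.

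**Step 3: check the 130 mmol/L criterion.** The treatment guidelines give it as ≤130. The sections on 24 to 48 hours, for both arms, speak of sodium reaching 130. If ≤130 is taken literally as an alternative to the 10–17 mmol/L rise, every enrolled patient meets it at entry, since 125 is below 130. A lower limit copied from that sentence could then have no effect at 48 h.

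**Step 4: size.** The article gives no rate for a rise ≥10 or <5 mmol/L, so the effect cannot be computed. As an illustration only, assume the 24 h rise is normal with mean μ and SD σ (values not in the documents). Then P(rise < c) = Φ((c − μ)/σ).

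| μ, σ | <10 (as defined) | 5 to <10 | <5 |
|---|---|---|---|
| 4, 3 | 97.7% | 34.7% | 63.1% |
| 4, 4 | 93.3% | 33.4% | 59.9% |
| 6, 3 | 90.9% | 53.9% | 36.9% |
| 6, 4 | 84.1% | 44.0% | 40.1% |
| 8, 3 | 74.8% | 58.9% | 15.9% |
| 8, 4 | 69.1% | 46.5% | 22.7% |

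Over this range, 16–63% of patients would meet the 24 h condition with a rise below the goal. The table shows that the missing limit can matter. It says nothing about a difference between arms.

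**The case against.** The best defence is that the outcome was meant as a safety ceiling, in line with the Background's limits on the rise. An upper-only definition is then coherent, and the fault is the label. That stands as far as it goes, and it is why renaming is an acceptable remedy. But the article uses target for the range to be attained, and under this name the result would be misread.

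A second defence is that no reader would apply a level below 10 mmol/L literally. I agree. That defect is editorial, though it recurs in the relowering trigger.

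Third, under-treatment is visible elsewhere: time to a rise of at least 5 mmol/L, time to sodium above 130 mmol/L, symptom and GCS change, and additional treatment. Both arms also continue or repeat treatment until the goal is met. This stands and limits the severity. None of these outcomes gives the share of patients who ended within the goals.

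Fourth, the outcome is not identical to relowering. One is a laboratory threshold and the other a treatment given, and the Discussion expects protocol violations from shift work. This also stands, so it is a near mirror and not a duplicate.

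A reader might go further and subtract the planning rates of 5% and 20% from 100%, to predict 95% v 80% on target. The documents do not support this. Those rates are for rises >12 or >18 mmol/L, whereas this outcome fails at ≥10 or ≥18. A patient with a 24 h rise of 11 mmol/L is neither overcorrected nor on target. Nor do they give any undercorrection rate from which to argue that the comparison between arms would shrink or reverse.

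**Conclusion.** The concern holds. On the evident reading, as a rise from the initial value, the outcome counts patients with no rise as on target, contrary to the article's own goals, and nothing elsewhere in the article repairs this. On the literal reading nobody can meet it.

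Severity is moderate. It is one secondary outcome, the primary outcome and the sample size do not depend on it, and other secondary outcomes partly reveal under-treatment. Its numerical effect cannot be determined from the article. The conclusion rests on the wording alone, and on the assumption that a rise from the initial value is what was meant.

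It would go too far to infer that the trial cannot detect under-treatment, or that the bolus arm would gain from this definition.

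**What to change.** 1. In Outcome measures and Statistical analyses, word the outcome as an increase from the initial serum sodium.
2. Align it with the article's own goals by adding their lower limits, and keep the upper limits applied at every sample within 24 h and within 48 h. Judging the range only at the 24 h and 48 h samples would pass an overshoot: a rise of 14 mmol/L at 12 h, relowered to 8 by 24 h, would look on target. State at which samples the lower limit is judged, and whether symptom relief is part of the outcome or stays with the symptom outcome.
3. Report under-, on- and over-target shares by arm.
4. If only a ceiling was intended, leave the limits, word them as an increase, and rename the outcome accordingly.

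Two reconciliations are for the trial team. The ≤130 mmol/L wording in the treatment guidelines must be reconciled with the 24-to-48-hour sections before the 48 h lower limit is written. The achieved-level wording of the relowering trigger, in the treatment guidelines and under Safety issues, must be reconciled with the wording as an increase elsewhere. This review does not choose the clinical limits.

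Cost: no new data, since sodium is already measured every 6 h for 2 days. The reported on-target rate will be lower if the lower limits are added. Recruitment began in August 2016, so this changes an outcome in a running open-label trial. It should be settled before the interim analysis and submitted to the Institutional Review Board and the registry, as Data and safety monitoring requires for revised procedures.
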